#### Definition of local control

FDG-PET response at 12 weeks will be defined as a complete metabolic response, partial metabolic response, stable metabolic disease or progressive metabolic disease based on visual assessment by the nuclear medicine physician’s report. Local control for patients will be assessed at 12 months as indicated by having no evidence of local disease on clinical (including endoscopic) examinations and imaging studies at 12 months. Tumour response will be assessed using Response Evaluation Criteria In Solid Tumors (RECIST) criteria version 1.1[39] which is the internationally recognised gold standard assessment method on the evaluation of therapeutic response in solid tumours.

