## Background

Mucosal primary head and neck cancer (MPHNC) has an estimated incidence of over 900,000 cases per year, and is associated with significant mortality, causing more than 350,000 deaths per year[1]. Organ preservation strategies involve the administration of a radical dose of radiation therapy, usually with concomitant chemotherapy, producing 5-year overall survival rates of between 30 and 50% [2]. Despite technical improvements in radiotherapy, significant toxicity may result from these treatments [3, 4].

Prognostication and treatment strategies are informed by clinical features [5] and increasingly by tumour biological features, notably preceding infection with oncogenic strains of human papilloma virus (HPV) [6, 7]. Reliable imaging biomarkers may therefore provide useful data to facilitate adaptive approaches including treatment intensification for poor responders and de-intensification for good responders [8]. Such strategies may improve the therapeutic ratio by reducing dose to organs at risk and increasing dose to areas harbouring subvolumes of more resistant tumour.

Positron-emission tomography using ^18^F–fluorodeoxyglucose (FDG-PET) is currently a standard investigation for initial staging of MPHNC. Retrospective studies have described FDG-PET’s performance in assessing disease following radical radiotherapy [9, 10] and its value in decision-making around surgical salvage has been demonstrated in a prospective trial [11]. Some limitations remain however, with the possibility of false-positive results due to benign tissue inflammation and of false-negative results due to limited spatial resolution.

Magnetic resonance imaging (MRI) has an established role in diagnosis and staging of MPHNC, and its use in radiotherapy planning continues to expand [12]. MRI has superior spatial resolution, better soft tissue definition and does not employ ionising radiation. Furthermore, functional sequences can provide additional information on tissue composition and biology which is not revealed by standard anatomical T1 and T2 weighted scans.

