### Objectives

#### Primary objective

To determine the correlation of pre-, during treatment and post-radiotherapy (± chemotherapy) functional MRI with tumour response at 3 months by FDG-PET scan and with local control at 12 months.

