### Endpoints

#### Primary endpoints

Correlation of functional MRI sequences with PET-CT at 3 months following treatment and local control at 12 months, including:Measurement of restricted water diffusion as on DWI, which can be a marker of high cellularity within a tumour, using ADC values, ΔADC and parameter maps of ADC.Measurement of tumour perfusion characteristics from DCE-MRI, using parameter maps and calculated values based on inflow and outflow (K^trans^, K_ep_) as well as degree of contrast enhancement of tissues (Relative Signal Intensity, RSI).Tumour size as defined on anatomical imaging using T2-weighted and/or T1-weighted Volume Interpolated Breathhold Examination (VIBE) Dixon MRI.

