### Subject selection

#### Inclusion criteria

18 years or olderHave the ability to give informed consentHistologically-proven invasive mucosal primary squamous cell carcinoma of head and neck region or patients with tumours strongly suspicious for mucosal primary head and neck cancer due to clinical features AND fine needle aspiration (FNA) cytology assessmentPrimary mucosal head and neck cancer (≥T2 and/or ≥N1) AND no evidence of metastatic disease on staging PET/CT or CT (chest ± abdomen ± pelvis)Patient undergoing curative intent primary radiotherapy ± chemotherapy

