#### Statistical analysis

Statistical analyses will be performed by using software SPSS and *p* < 0.05 will be considered statistically significant. Chi-square test will be used to compare the prevalence of FDG-PET CMR between MRI-positive and negative groups. Comparisons of the ADC values/maps of pre-, intra- and post-treatment DWI images will be performed by using one way analysis of variance (ANOVA) test. Comparisons of the DCE parameters such as K^trans^, K_ep_, area under the curve (AUC) at initial 60 and 90 s of pre-, intra- and post-treatment will be performed by using the Kruskal-Wallis test. To determine the sensitivity and specificity of DWI and DCE parameters for FDG-PET CMR and 12 month local control, Kappa association statistics will be used. Receiver operator characteristics (ROC) will be used to obtain an optimal threshold for individual MRI parameters.

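### Local control is defined by disease status at 12 months only, so a local failure cleared by salvage before then counts as controlled

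*Protocol article*

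**What the plan says.** The Primary objective relates "functional MRI with tumour response at 3 months by FDG-PET scan and with local control at 12 months". The Primary endpoints section repeats the pairing: "Correlation of functional MRI sequences with PET-CT at 3 months following treatment and local control at 12 months".

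The section Definition of local control supplies the rule: "Local control for patients will be assessed at 12 months as indicated by having no evidence of local disease on clinical". Endoscopy forms part of that assessment, and imaging at the same time point is needed as well. The same section adds that tumour response is assessed by RECIST 1.1. It mentions neither local disease found and treated before month 12 nor patients who do not reach month 12.

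The Statistical analysis section treats the outcome as binary: "To determine the sensitivity and specificity of DWI and DCE parameters for FDG-PET CMR and 12 month local control, Kappa association statistics will be used".

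Salvage surgery appears only in the Background, where the article says of FDG-PET that "its value in decision-making around surgical salvage has been demonstrated in a prospective trial". Laryngectomy appears once, in the Toxicity list of late effects, with no link to local failure.

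**The concern.** The first hypothesis is that functional MRI predicts response to radiotherapy with or without chemotherapy. The matching outcome is whether that treatment controlled the primary site. Status on one later date is a different quantity, because it also reflects whatever was done after the treatment failed.

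A patient with residual or recurrent primary-site disease that is removed before month 12 has no evidence of local disease at month 12 and so meets the definition. If MRI had flagged that patient as a poor responder, a correct prediction would be recorded as an error. At stake is the second component of the primary endpoint and the accuracy and agreement statistics reported for it.

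**Working it through.** **Reading the rule.** Consider three patients, with time counted from the end of treatment.

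| Course | Status at 12 months | Scored under the rule |
|---|---|---|
| Never any local disease after radiotherapy | No evidence of disease | Controlled |
| Local failure, not cleared | Disease present | Not controlled |
| Local failure, cleared by salvage before month 12 | No evidence of disease | Controlled |

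The first and third patients get the same code, although radiotherapy failed in the third. The RECIST sentence concerns tumour response and does not separate them. DFS and OS are separate secondary outcomes and leave this coding unchanged.

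**The plan's own figure.** The only sample-size figure is 55, for CMR of 87% against 51% at 80% power and 5% significance. A two-sided calculation with pooled variance and no continuity correction gives 50 in total at 1:1 and 53 at 40:60, so 55 is sound. It covers the PET comparison only. No target is stated for local control, so this point contradicts no stated figure.

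**Effect of the coding.** Inputs, all assumed except the total of 55: 28 MRI-positive patients (good response) with true local failure 10%, and 27 MRI-negative patients with 40%. A share s of failures is salvaged by month 12, equal in both groups. An MRI-negative result is taken as the test for failure.

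- Observed failure in each group = true failure × (1 − s), so the difference = 30 points × (1 − s) and the risk ratio stays at 40/10 = 4.
- Sensitivity = failures in MRI-negative ÷ all failures. The factor (1 − s) cancels: 10.8/(10.8 + 2.8) = 79.4% for every s.
- Specificity = controlled in MRI-positive ÷ all controlled.
- Kappa = (observed − chance agreement)/(1 − chance agreement).

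| s | Failures, MRI-positive + MRI-negative | Difference | Sensitivity | Specificity | Kappa | Local control overall |
|---|---|---|---|---|---|---|
| 0 | 2.8 + 10.8 | 30 points | 79.4% | 25.2/41.4 = 60.9% | (0.6545 − 0.5046)/0.4954 = 0.30 | 41.4/55 = 75.3% |
| 30% | 1.96 + 7.56 | 21 points | 79.4% | 26.04/45.48 = 57.3% | (0.6109 − 0.5059)/0.4941 = 0.21 | 45.48/55 = 82.7% |
| 50% | 1.4 + 5.4 | 15 points | 79.4% | 26.6/48.2 = 55.2% | (0.5818 − 0.5068)/0.4932 = 0.15 | 48.2/55 = 87.6% |

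If local control rather than local failure is taken as the target condition, the labels sensitivity and specificity swap; the numbers do not change.

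**A second assumed starting point.** If true local control equalled the CMR rates (87% against 51%), salvage of 10%, 20% or 30% of failures would shrink the 36-point difference to 36 × 0.9 = 32.4, 36 × 0.8 = 28.8 or 36 × 0.7 = 25.2 points.

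**Unequal salvage.** If only MRI-negative failures were salvaged, at 50%, the difference would be 20 − 10 = 10 points and sensitivity 5.4/8.2 = 65.9%. If only MRI-positive failures were, it would be 40 − 5 = 35 points and 10.8/12.2 = 88.5%. The direction therefore depends on a pattern the documents do not give.

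**The case against.** The strongest reply is that the definition is silent on salvage rather than wrong about it, and that intercurrent surgery, deaths and losses are often left to an analysis plan. For deaths and losses this largely stands. No exclusion is stated, and withdrawn patients stay in follow-up and analysis unless they ask otherwise. A reader might infer that early deaths are dropped selectively; the text supports only that no handling rule is given. One-year DFS and OS also keep those deaths in view. For salvage the reply fails: the article gives a working rule for a primary outcome, and that rule classifies the salvaged patient.

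Other stronger readings are tempting but unsupported:

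- **Lost power.** Any power figure for local control would rest on assumed rates and on a chi-square test that the article assigns only to CMR. No stated power is lost.
- **Biased sensitivity.** Under equal salvage, sensitivity does not move.
- **PET-driven misclassification.** It is plausible that the 3-month PET directs patients to salvage, but this is inferred from a Background sentence about another trial. No salvage pathway, timing or rate is given for this cohort.
- **Nodal disease.** Eligibility includes node-positive patients, but the protocol chose local control and does not say which sites are contoured. That the imaged tumour is a node in some patients is conjecture.

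**Conclusion.** The point holds for the definition. As worded, local control at 12 months includes patients whose local failure was cleared before that date, which does not fit the stated aim of predicting response to radiotherapy with or without chemotherapy. With equal salvage in both MRI groups, the absolute contrast shrinks by the factor (1 − s) and specificity for failure falls, while sensitivity and the risk ratio are unchanged. In the first illustration, s of 30% to 50% costs 9 to 15 points of difference and 3.6 to 5.7 points of specificity. Those figures rest on assumed failure and salvage rates and show only the form of the effect; the documents do not allow its size to be stated.

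The missing rule for deaths and losses is a lesser gap to close in the same sentence. The definition should be fixed before the local-control analysis; the 3-month PET comparison is not affected.

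**What to change.** Replace the status rule with an event rule, for example: local failure is any documented persistent or recurrent disease at the primary site between the end of radiotherapy and 12 months, regardless of later salvage or later status; local control is freedom from such failure. In the same sentence, state that patients who die or are lost before 12 months without local failure are not counted as controlled by default. They could be treated as a competing event (death) or censored (loss), or as non-evaluable with a sensitivity analysis. In 55 patients a competing-risk analysis is optional; a binary rule is enough to cure the problem.

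The cost is one definition, with no added patients. The reported local-control rate will be somewhat lower: 75.3% instead of 82.7% or 87.6% in the illustration. Failure dates must be captured. Visits at 1, 3, 6 and 12 months are listed, but for quality of life, toxicity and swallowing. The listed MRI and PET scans end at 3 months, and the schedule figure was not available here. The sponsor should therefore confirm that local disease findings and salvage procedures between 3 and 12 months are recorded with dates.

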#### Statistical analysis

Statistical analyses will be performed by using software SPSS and *p* < 0.05 will be considered statistically significant. Chi-square test will be used to compare the prevalence of FDG-PET CMR between MRI-positive and negative groups. Comparisons of the ADC values/maps of pre-, intra- and post-treatment DWI images will be performed by using one way analysis of variance (ANOVA) test. Comparisons of the DCE parameters such as K^trans^, K_ep_, area under the curve (AUC) at initial 60 and 90 s of pre-, intra- and post-treatment will be performed by using the Kruskal-Wallis test. To determine the sensitivity and specificity of DWI and DCE parameters for FDG-PET CMR and 12 month local control, Kappa association statistics will be used. Receiver operator characteristics (ROC) will be used to obtain an optimal threshold for individual MRI parameters.

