## Methods

### Study design and consent

This study is a prospective single arm observational trial of patients undergoing curative intent primary radiotherapy, with or without chemotherapy, for MPHNC at Liverpool and Campbelltown Hospitals. Patients are identified and evaluated by the multidisciplinary team. Informed consent is obtained by medically trained personnel as per the trial delegation log. Administrative support, including travel funding for study scans, is provided by clinical trials unit staff.

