### Imaging

#### Imaging schedule

Functional MRI studies are carried out prior to commencing treatment, then weeks 2, 3, 5 and 6 during treatment, followed by 1 month and 3 months post-treatment (Fig. 1).

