### Statistical plan

#### Sample size determination

Based on our previous study using week 3 FDG-PET scan in head and neck cancer patients, the following sample size calculation is made. To test a significant FDG-PET complete metabolic response (CMR) rate of 87% in the MRI-positive group versus an FDG-PET CMR rate of 51% in the MRI-negative group, the study will need to recruit 55 patients in total to reach 80% power (at 5% significance level). This number is based on an assumption that the MRI-positive group and MRI-negative group will be balanced (e.g. 50%:50% but is powered to allow up to a 40%:60% biased ratio). It is anticipated that recruitment will be completed in 24 months. Patients will be offered participation in the “hop on hop off” sub-study, with a recruitment goal of 20.

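### The time-course comparisons of ADC and DCE parameters use tests for independent groups on repeated scans of the same patients; the p-values are not valid, and the power loss ranges from slight to large

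*Protocol article*

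**What the plan says.** - **Design** (Study design and consent): "This study is a prospective single arm observational trial of patients undergoing curative intent primary radiotherapy". There is one group of patients and no parallel group.
- **Scans** (Imaging schedule): "Functional MRI studies are carried out prior to commencing treatment, then weeks 2, 3, 5 and 6 during treatment". Two more follow, at 1 and 3 months after treatment, so up to seven per patient.
- **Test for ADC** (Statistical analysis): "Comparisons of the ADC values/maps of pre-, intra- and post-treatment DWI images will be performed by using one way analysis of variance (ANOVA) test".
- **Test for DCE parameters** (same section): Ktrans, Kep and the area under the curve "pre-, intra- and post-treatment will be performed by using the Kruskal-Wallis test".

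The article names no repeated-measures, mixed-model, Friedman or other paired method. It gives no SD, within-patient correlation or expected change for any MRI parameter. The sample size rests on another comparison: complete metabolic response (CMR) on PET in MRI-positive against MRI-negative patients, by chi-square.

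**The concern.** One-way ANOVA and Kruskal-Wallis ask whether separate, independent samples differ. Here the samples are treatment phases, and the same patients supply each one. Stable differences between patients, such as a tumour with high ADC throughout, are counted as noise although each patient could serve as his or her own control.

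At stake is the validity of every reported p-value for change over treatment. With one group per scan time the error is on the cautious side, so a real change in ADC or perfusion may be reported as non-significant. This is not detail left to an analysis plan. The article names the tests, and those named do not fit the design.

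**Working it through.** **1. The plan's own figure.** Inputs from Sample size determination: CMR 87% vs 51%, 80% power, 5% level (taken as two-sided), split 50:50 down to 40:60. With k = n2/n1 and p̄ the pooled rate:

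n1 = [1.96·√((1+1/k)·p̄(1−p̄)) + 0.8416·√(p1q1 + p2q2/k)]² / (p1−p2)²

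- 50:50: p̄ = 0.69. (1.282 + 0.507)²/0.1296 = 24.7, so 25 per group and 50 in total.
- 40:60 (k = 1.5): p̄ = 0.654. (1.204 + 0.445)²/0.1296 = 21.0, so 21 + 32 = 53.

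At N = 55 the power is 84% (50:50) or 82% (40:60). The stated 55 is reproduced. It uses one MRI classification per patient, so the repeated scans do not enter it.

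**2. Size of the distortion, analytically.** Let σ² be the variance across patients at one scan and ρ a constant within-patient correlation. The one-way error mean square estimates σ². The within-patient error mean square estimates σ²(1−ρ). Hence F(one-way) ≈ (1−ρ)·F(within-patient).

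With 55 patients and 7 scans the within-patient test has 6 and 54×6 = 324 degrees of freedom, and its 5% critical value is 2.127. The one-way test has 6 and 7×54 = 378. A result exactly at the correct p = 0.05 would be reported as:

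| ρ | one-way F | reported p |
|---|---|---|
| 0.3 | 1.489 | 0.18 |
| 0.5 | 1.063 | 0.38 |
| 0.7 | 0.638 | 0.70 |

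**3. Type I error by simulation** (55 patients, 7 complete scans, each scan a group, normal data, 4,000 data sets; ρ and its structure are assumptions). Nominal level 5%:

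| ρ = 0.3 / 0.5 / 0.7 | constant correlation | AR(1) |
|---|---|---|
| one-way ANOVA | 0.7 / 0.03 / 0% | 3.3 / 2.2 / 1.0% |
| Kruskal-Wallis | 0.6 / 0.05 / 0% | 3.0 / 2.1 / 1.2% |
| repeated-measures ANOVA (Greenhouse-Geisser) | 4.4 / 3.8 / 4.9% | 4.3 / 4.2 / 5.3% |

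A repeat with 20,000 data sets gave 0.7 / 0.02 / 0% and 3.7 / 2.4 / 0.9% for one-way ANOVA.

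**4. Power.** A linear drift over the seven scans is assumed, in units of the SD across patients at one scan. For a total drift of 0.4 SD, one-way against repeated-measures ANOVA:

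| ρ | constant correlation | AR(1) |
|---|---|---|
| 0.3 | 34% vs 61% | 40% vs 43% |
| 0.5 | 23% vs 77% | 35% vs 44% |
| 0.7 | 13% vs 95% | 30% vs 51% |

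As a share of the attainable power, the loss is 44%, 70% and 86% under constant correlation (for example (61−34)/61 = 44%), and 7%, 20% and 41% under AR(1). Repeat runs agree within about two points. At a drift of 1 SD both tests reach at least 99.6% in all six settings.

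**5. If scans are pooled into three phases** (1, 4 and 2 scans per patient). Under constant correlation the one-way type I error is 1.7 / 0.25 / 0%. Under AR(1), a check with 10,000 data sets gave 6.6 / 6.0 / 4.3%, because neighbouring scans in one phase are then counted as independent. Pooling does not repair the test, and the direction of the error is then no longer assured.

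**The case against.** **"One way ANOVA" may be shorthand for one-way repeated-measures ANOVA.** That is possible for ADC, though the text does not say it. It does not help the DCE half: Kruskal-Wallis is an independent-samples test, and its paired counterpart is Friedman.

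**The error is mostly conservative and the comparison is supportive.** This stands. The primary objective concerns association with PET response and local control. No objective asks simply whether ADC or Ktrans changes over time.

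**The size is not knowable from the documents.** This also stands. A reader might infer that most of the power is lost. In the table above that is true in two of six settings. Scans run from before treatment to 3 months after it, so correlation that fades with time is at least as plausible as constant correlation.

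**The tests are not tied to the timing objective.** A reader might infer that the secondary objective on the best time for MRI fails because these tests pool responders and non-responders. The article does not assign them to that objective. It also names chi-square, sensitivity and specificity, and ROC analyses that relate MRI to outcome and could be run at each scan time.

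**Conclusion.** The point holds for the time-course comparisons of ADC and DCE parameters, and only there. Tests for independent groups are named for serial scans of the same patients, and nothing else in the article corrects this. With each scan time as a group and positive within-patient correlation, the p-values are too large. Only under pooling into phases with fading correlation did the error rate come out near or slightly above 5%.

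The mismatch itself needs no assumption. Its size rests on an assumed correlation, correlation structure and drift, with complete data on all 55 patients: from a loss of a few points of power to nearly all of it.

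A reader might also infer that the primary analysis or the sample size is compromised. Neither is. The chi-square comparison uses each patient once, and the 55 patients are reproduced. The correction is worth making before analysis but is not a must-fix for the primary analysis.

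**What to change.** In Statistical analysis, replace both tests with a within-patient method. Either of these cures the defect:

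- **Linear mixed model** for ADC and for each DCE parameter, with patient as random effect, scan time as a categorical factor, and DCE values log-transformed where skewed. State the covariance structure, because a random intercept alone implies constant correlation. This option also keeps patients who miss a scan.
- **Repeated-measures ANOVA** with a sphericity correction for ADC, and **Friedman** for the DCE parameters, both on patients with complete scans. Friedman was somewhat liberal in the simulation when correlation faded with time (7.0% under AR(1) at 0.7).

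State whether time enters as seven scans or three phases. A time-by-response term is an optional addition. It tests whether trajectories differ between responders and non-responders, and does not by itself settle which scan time is best.

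The cost is a few lines of text. No further patients or scans are needed, and SPSS, the software already named, fits these models.

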## Discussion

In recent years intensity-modulated RT, along with advanced diagnostic and on-treatment imaging technologies, have improved the therapeutic ratio in head and neck cancer [41]. The enhanced ability to dose-paint and the recognition of heterogeneity within tumours gives rise to the promise of functional image-guided RT (fIGRT), where subvolumes may be treated to differing doses according to imaging-derived parameters. Longitudinal diffusion-weighted imaging has already been shown to be feasible in MRI-guided cobalt radiotherapy systems [42], suggesting that the addition of functional as well as anatomical imaging may serve to improve outcomes with these systems, as well as in the MRI-guided linear accelerators in development.

Our protocol builds on our earlier work which established the feasibility of serial functional MRI during a course of treatment for MPHNC. Refinements to the imaging protocol include the addition of DCE sequences, which may be expected to add further value [43], and the expansion of the BOLD sequence to acquire multiple slices across a volume, an imaging technique which may be more reliable than BOLD imaging carried out on single slices [44]. The additional information gained from the enhanced suite of imaging sequences in the current study will help to define which sequences, at which time points, can be used to adapt and personalise radiotherapy treatment. This information will then feed into the design of interventional studies of adaptive RT.

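### The stated analyses do not serve the best-scan-time objective: the between-time tests ignore outcome, and the outcome-linked tests do not compare scan times

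*Protocol article*

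**What the plan says.** Under Secondary objectives, the protocol article asks for the best time during radiotherapy to perform MRI for assessing tumour response and local control. The abstract repeats this aim. Under Imaging schedule: "Functional MRI studies are carried out prior to commencing treatment, then weeks 2, 3, 5 and 6 during treatment", followed by two post-treatment scans. Weeks 2, 3, 5 and 6 are therefore the four candidate times.

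Under Statistical analysis, two tests compare scan times:
- For ADC: "Comparisons of the ADC values/maps of pre-, intra- and post-treatment DWI images will be performed by using one way analysis of variance (ANOVA) test".
- For DCE parameters, the comparison "of pre-, intra- and post-treatment will be performed by using the Kruskal-Wallis test".

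Three analyses use the outcome:
- A group comparison: "Chi-square test will be used to compare the prevalence of FDG-PET CMR between MRI-positive and negative groups".
- A cut-off for each measure: "Receiver operator characteristics (ROC) will be used to obtain an optimal threshold for individual MRI parameters".
- An agreement measure against both outcomes: "To determine the sensitivity and specificity of DWI and DCE parameters for FDG-PET CMR and 12 month local control, Kappa association statistics will be used".

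The Discussion gives the answer a use: the imaging data "will help to define which sequences, at which time points, can be used to adapt and personalise radiotherapy treatment", and this is to inform later interventional studies of adaptive radiotherapy.

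**The concern.** The best time to scan, for this objective, is the time at which the MRI value best separates patients who will respond, or stay locally controlled, from those who will not. That is a comparison of discrimination between weeks. A test of whether values differ between scan times asks a different question. A parameter can drift strongly in every patient and say nothing about who responds, or it can separate responders well at one week while its average hardly moves.

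Repeated-measures modelling would deal with the fact that the same patients are scanned up to seven times, which is a separate matter. It would not solve this problem, because the quantity estimated would still be the time course of the values.

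At stake is a secondary result meant to guide the design of later trials. If the question is left to an informal look at four ROC results, the leading week will be chosen partly by chance and its accuracy will be overstated.

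**Working it through.** **1. Stated analyses against the objective**

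| Analysis | Compares scan times? | Uses outcome? |
|---|---|---|
| One-way ANOVA (ADC) | yes | no |
| Kruskal-Wallis (DCE) | yes | no |
| Chi-square, CMR by MRI group | no scan time named | yes |
| Kappa, for CMR and 12-month local control | no | yes |
| ROC, for a threshold | no | yes |

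The objective needs one row with yes in both columns, and there is none.

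**2. The plan's own figure.** The article gives no figure for the timing objective, only N = 55 for the chi-square comparison. With CMR rates of 0.87 and 0.51, a 40:60 split (k = 1.5), two-sided 5% (assumed, as sidedness is not stated) and 80% power:

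n1 = [1.96·√((1 + 1/k)·p̄(1 − p̄)) + 0.842·√(p1(1 − p1) + p2(1 − p2)/k)]² / (p1 − p2)²

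- p̄ = (0.87 + 1.5 × 0.51)/2.5 = 0.654.
- n1 = (1.204 + 0.445)²/0.1296 ≈ 21, so the total is 21 + 32 = 53.
- N = 55 gives 82.0% power at this split. The sample size is sound and not at issue.

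**3. Does the between-time test carry information on discrimination?** This used 2000 simulated trials of 55 patients with seven scans. The drifts, separations and within-patient correlation (0.6) are assumptions.

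- Values drift over treatment (0.3 to 1.0 SD from baseline across weeks 2 to 6) and no scan separates responders (AUC 0.50 throughout): ANOVA is significant in 100% of runs.
- No drift, with real separation at week 3 (AUC 0.80, against about 0.59 at the other on-treatment weeks): ANOVA is significant in 0% of runs, while the highest AUC falls at week 3 in 99%. Part of the 0% comes from treating correlated scans as independent.

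The two questions can thus have opposite answers.

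**4. Cost of an informal choice by highest AUC.** At a 50:50 split the CMR rate is (0.87 + 0.51)/2 = 0.69, and 0.69 × 55 ≈ 38 responders and 17 non-responders. Assume normal markers, equal separation of 0.7 SD at all four weeks, AUC = Φ(0.7/√2) = 0.69, and a common between-week correlation. Results from 4000 runs each:

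| Between-week correlation | SE of a paired AUC difference | Overstatement of the highest AUC |
|---|---|---|
| 0.3 | 0.09 | 0.07 |
| 0.6 | 0.07 | 0.05 |
| 0.8 | 0.05 | 0.04 |

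Hand check: the expected maximum of four exchangeable normal estimates exceeds their mean by about 1.03 × SE(difference)/√2. At correlation 0.6 this is 1.03 × 0.072/1.414 = 0.052, in agreement.

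**5. Precision when the weeks do differ.** Assume separations of 0.6, 0.9, 0.6 and 0.4 SD at weeks 2, 3, 5 and 6, giving AUCs of 0.66, 0.74, 0.66 and 0.61. The highest observed AUC then falls on the truly best week in 74% of trials (64% at correlation 0.3, about 86% at 0.8). The week 3 minus week 6 difference is 0.74 − 0.61 = 0.13. With an SE of 0.07, the 95% half-width is 1.96 × 0.07 = 0.14.

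**The case against.** The strongest reply is that the article never assigns ANOVA or Kruskal-Wallis to the timing objective. Describing how ADC and DCE values move through treatment is a legitimate aim in itself. The primary objective already correlates MRI before, during and after treatment with 3-month PET response and 12-month local control, so ROC at each scan lies within the plan's scope. A full protocol or analysis plan, not shown here, may add the comparison.

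Much of this stands. A reader might infer that the plan would name the week with the largest average change as best, and so reach a wrong answer. The documents do not support that: they contain no such rule, an omnibus test selects no week, and the text speaks only of pre-, intra- and post-treatment. A simulation can put the largest change on the worst week in over 90% of trials, but only by assuming both that rule and the drift pattern. Nor can one say that the objective could not be addressed at all, since informal week-by-week ROC is possible.

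What the reply does not remove is the gap in the table of analyses. The article lists its tests by name and purpose; its between-time tests omit outcome, and its outcome-linked tests omit a between-time comparison. ROC is given one purpose, a threshold. The concern is the mismatch between the tests stated and the objective stated, not missing detail.

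**Conclusion.** The point holds in this limited form: the analyses stated cannot rank weeks 2, 3, 5 and 6 by how well MRI separates responders, which is what the secondary objective asks. This follows from the structure of the tests and needs no numerical assumption.

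The size of the consequence does rest on assumptions. If the four weeks are equally good, an informal choice of the highest AUC overstates it by about 0.05 (0.04 to 0.07). This assumes normal markers, 38 responders among 55 patients, a true AUC of 0.69 and between-week correlations of 0.8 to 0.3. Only N = 55 and the 69% response rate derive from the article. It gives no rate for 12-month local control, so precision for that outcome cannot be judged from it.

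The primary chi-square comparison and the sample size are unaffected. The change is worth making before analysis, because the result is meant to inform later trials and the remedy needs no new data.

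**What to change.** For the timing objective, state the following analysis:

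- Estimate the AUC for CMR, and separately for 12-month local control, of each MRI parameter or its change from baseline at weeks 2, 3, 5 and 6, in the same patients.
- Report paired AUC differences between weeks, with intervals from a bootstrap that resamples patients.
- Report the ranking of the weeks with its uncertainty, and an optimism-corrected AUC for the leading week.
- Keep ANOVA and Kruskal-Wallis as description of the time course only.

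Do not require every paired difference to exclude zero before reporting a leading week. In the unequal-weeks setting of step 5 of the working, such a rule would name week 3 in only about 6% of trials at correlation 0.6 (about 3% at 0.3 and 12 to 13% at 0.8).

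The cost is analysis-plan wording and programming, with no new scans or patients. The downside is wide intervals: an SE of about 0.05 to 0.09 for an AUC difference means 95% half-widths of roughly 0.10 to 0.18, so the trial may have to report that the weeks could not be separated.
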